### v) Outcomes

Six outcomes will be measured in this study: (a) knowledge of PSA and prostate cancer-related issues – this is the main outcome of the study, on which the sample size calculation is based; (b) attitudes to testing; (c) decision conflict; (d) anxiety; (e) intention to undergo PSA testing; (f) uptake of the PSA test. Outcomes (a) – (e) will be gathered from the online questionnaire. In addition to these outcomes, based on these results, a mathematical simulation model of the effects of *Prosdex *on subsequent resource use and health outcomes will also be developed. This model will be based on the results of the trial.

#### a) Knowledge of PSA and prostate cancer-related issues

Knowledge will be the principal outcome of this study. Previous randomised controlled trials of PSA decision aids have used knowledge as their principal outcome, and in our systematic review of these trials we found that PSA decision aids resulted in an improvement in knowledge of 19.5% [11]. Knowledge will be assessed using a set of knowledge questions, used in our earlier evaluation of a brief paper-based leaflet about PSA testing,[12] which showed an ability to discriminate between intervention and control groups.

#### b) Attitudes to testing

This will use a 12-item scale developed and used in the same evaluation of a brief paper-based leaflet about PSA testing [12].

#### c) Decision conflict [13]

This scale measures patients' confidence or uncertainty ('conflict') about whether they feel their choice is the best for them personally. It has acceptable validity and reliability (internal consistency alpha coefficients range from 0.78 – 0.89; test-retest reliability coefficients exceed 0.80) [14]. Given the nature of the decision about having a PSA test, with a high degree of uncertainty likely to affect decision making, it is important to use this, the most widely used outcome measure in decision aid studies [15].

#### d) Anxiety

This will be assessed using the short form Spielberger questionnaire for 'state' anxiety, validated and shown to be responsive in our earlier studies of shared decision making and risk communication [10].

#### e) Intention to undergo PSA testing

This will be assessed using a single item question, with Likert-like response scale, which has also been used in our earlier evaluation of a brief paper-based leaflet about PSA testing [12].

#### f) Uptake of the PSA test

This will be assessed at six months after the intervention. GPs who participate in the study will be asked to ascertain the men's PSA testing status for that six month period, from their records, and inform the research team whether or not the test was done. The GPs will be provided with specific forms for this purpose, to be returned to the research team. It is possible that men may have had PSA tests elsewhere, such as via hospital clinics, but it is likely that these will be evenly distributed across the intervention and control groups. Moreover, it may be less likely that these decisions to be tested were patient-led. Such 'external' results, when they do occur, are increasingly recorded in GP records.

### (vi) Comparisons and analysis

Comparability of the four groups for baseline characteristics of age, ethnicity, marital status and education will be assessed. Outcomes will be compared between groups on an 'intention to treat' basis by standard statistical tests, including chi^2 ^for categorical variables and t, Mann-Whitney and one-way ANOVA tests for continuous and ordinal variables. Point and interval estimates for appropriate measures of effect size will be reported as well as p values. A clinically significant and relevant difference in the principal outcome, knowledge, between the two groups, will be set at 20%. The statistical power for this study is aimed at 90%, assuming a type 1 error rate of 5%. The sample size will be 600 men: 150 in each of the four groups. This figure is derived from the findings of our systematic review of PSA decision aids where 4 RCTs (USA) were found to result in improved knowledge of 19.5% (SD 45.1). Thus, 150 men per group will allow the detection of a 20% absolute difference with over 90% power. Assuming a recruitment and completion rate of 30%, 2000 men will be invited from 20 GP practices, 100 men from each practice. For the Decisional Conflict Scale, a comparison of any 2 groups each of 150 subjects would detect a shift of 0.32 standard deviations, with power 80% at the conventional 5% alpha level. The data will be collected in a SQL-server database, transferred to Excel, and then analysed using SPSS Syntax, and the results expressed with both p values and confidence intervals.

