#### c) Recruitment process

Suitable men will be identified by GPs, in Wales, who will also send the invitation letters, participant information sheets (PIS) and consent forms. A member of the practice staff, probably the data manager, will be asked to identify men, aged 50–75, who have not had a PSA test. Using that generated list, the data manager will be asked to select 100 men using a serial recruitment process based on the date of the month of the men's birthdays: that is, the first man selected will be the first man on the list with a birthday 01/month/year; second man, 02/month/year; and so forth up to 31 when the process will be repeated until 100 men are selected. A member of the practice staff who has knowledge of the patients – Practice Manager or GP – will then be asked to screen the list for men who, in their opinion, are unsuitable for the trial due to serious ill-health. The number of men thus removed will be reported.

Affirmative consent forms from each practice will be transferred to the research officer who, in turn, will allocate each participant from that practice with a number provided the by trial statistician who will oversee the allocation process. Accordingly, the participants will be randomly allocated, by computer, to one of two intervention groups or to one of two control groups. This process will occur remotely in order to secure concealment. For each practice, the statistician will allocate 80 numbers, generated in 'blocks', the number for which will be between 12 and 16 in order to guarantee 'balance'. Randomisation will occur at the level of the man as we are interested in individual decision-making outcomes, and there is unlikely to be a significant intra-cluster correlation for these outcomes [10]. There will be no randomisation of the GP practices, but they will be stratified according to socio-economic groups, with an aim of 4 different such groups. After the collection of the data, there will be social analysis of these groups.

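### The named tests leave out practice, within which men are randomised, and the recorded age and education; they are valid, but possibly conservative and less precise than an adjusted analysis would be

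*Protocol article*

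**What the plan says.** **Randomisation** (Methods iii, c, Recruitment process). Men are randomised individually, but the numbers are produced practice by practice: "For each practice, the statistician will allocate 80 numbers, generated in 'blocks', the number for which will be between 12 and 16". The section justifies individual randomisation partly by stating that "there is unlikely to be a significant intra-cluster correlation for these outcomes", and gives no figure. Practices are not randomised; "they will be stratified according to socio-economic groups, with an aim of 4 different such groups", with a later social analysis of those groups.

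**Analysis** (Methods vi, Comparisons and analysis). Groups are compared "by standard statistical tests, including chi"-squared for categorical variables and "t, Mann-Whitney and one-way ANOVA tests for continuous and ordinal variables". Effect estimates with intervals are promised. The only role given to the recorded baseline variables is this: "Comparability of the four groups for baseline characteristics of age, ethnicity, marital status and education will be assessed". No practice, stratum or covariate term is named for any outcome.

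**Timing of measurement** (Methods iv, Intervention). The questionnaire is first completed after the intervention, and control group B first completes it at six months. No pre-intervention score for knowledge or the other scales is described.

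**Power** (Methods vi). For knowledge, "150 men per group will allow the detection of a 20% absolute difference with over 90% power", using an SD of 45.1. For decisional conflict, a shift of 0.32 SD is to be detected with 80% power.

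**The concern.** Two separate things are at issue.

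1. **Practice.** Blocking within practice removes between-practice differences from the comparison of groups. A t-test or chi-squared test does not know this and leaves those differences in its standard error. If outcomes vary by practice, the standard error is too large and the test rejects less often than its nominal 5%.

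2. **Age and education.** These are not randomisation factors, so for them nothing is mismatched: the unadjusted standard error is right for the unadjusted estimate. Adjustment would instead give a more precise estimate if they predict the outcome, and the article records them without using them that way.

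What is at stake is efficiency. It matters most where there is no spare power. Decisional conflict is planned at only 80%, and Prosdex against the paper version, one of the two main comparisons, sets nearly identical content side by side. Checking comparability with no prespecified adjustment also leaves open what would be done if an imbalance appeared.

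**Working it through.** **Inputs from the article.** 150 men per group; knowledge difference 20 points, SD 45.1; alpha 5%, taken as two-sided (the article does not say); decisional conflict shift 0.32 SD; 20 practices; 600 men, hence 600/20 = 30 per practice.

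**Assumed.** R², the share of outcome variance explained jointly by practice, age and education, from 0 to 0.20; ICC from 0 to 0.20. The article gives neither.

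**Step 1: the plan's own figures.** Power = Φ(difference/SE − 1.96), with SE = SD × √(2/150).
- Knowledge: SE = 45.1 × 0.1155 = 5.21. 20/5.21 = 3.84, and Φ(1.88) = 97.0%. The claim of over 90% is met.
- Decisional conflict: 0.32/0.1155 = 2.77, and Φ(0.81) = 79.1%. This agrees with 80% to within a point.

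**Step 2: gain from adjustment on a continuous scale.** SE ratio = √(1 − R²); equivalent n per group = 150/(1 − R²); 95% half-width for knowledge = 1.96 × 5.21 × √(1 − R²).

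| R² | SE ratio | Equivalent n | Half-width, knowledge (points) | Power, knowledge, 20 points | Power, decisional conflict, 0.32 SD |
|---|---|---|---|---|---|
| 0 | 1.00 | 150 | 10.2 | 97.0% | 79.1% |
| 0.05 | 0.975 | 158 | 9.9 | 97.6% | 81.2% |
| 0.10 | 0.949 | 167 | 9.7 | 98.2% | 83.2% |
| 0.20 | 0.894 | 188 | 9.1 | 99.0% | 87.3% |

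**Step 3: the practice term alone.** Simulation with 20 practices of 30 men, four groups, blocks of 12 or 16 within practice (reading the article's 12 to 16 as block size), total SD 1, 4,000 runs per ICC. Two groups were compared by t-test and by a linear model with practice effects.

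| ICC | Type I error, t-test | Type I error, model | Power for 0.32 SD, t-test | Power for 0.32 SD, model |
|---|---|---|---|---|
| 0 | 4.8% | 5.0% | 78.8% | 78.9% |
| 0.01 | 5.5% | 5.5% | 80.1% | 79.9% |
| 0.05 | 4.4% | 4.8% | 79.3% | 80.3% |
| 0.10 | 3.9% | 4.8% | 80.5% | 82.8% |
| 0.20 | 3.2% | 4.7% | 81.4% | 85.8% |

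Monte Carlo standard errors are about √(0.05 × 0.95/4000) = 0.3 points for type I error and √(0.8 × 0.2/4000) = 0.6 points for power, so the first two rows show no measurable difference.

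**Step 4: cross-check of the conservatism.** With perfect balance within practice, the t-test's type I error is 2 × [1 − Φ(1.96/√(1 − ICC))]. ICC 0.05: 1.96/0.975 = 2.01, giving 4.4%. ICC 0.10: 1.96/0.949 = 2.07, giving 3.9%. Both agree with the simulation.

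**Step 5: PSA uptake.** The √(1 − R²) rule belongs to linear models. Adjusted logistic regression estimates a conditional odds ratio, a different quantity, whose interval does not narrow in this way. No figure is therefore given for uptake.

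**The case against.** The other side has a good case.

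- **The list of tests is open.** It is introduced by a word meaning that others may follow, and a fuller plan could add adjusted models. That stands in part. But every test named is unadjusted, the covariates are assigned a different task, and nothing signals an adjusted analysis.
- **The article expects a negligible ICC.** If so, the practice term gains almost nothing, as the rows for ICC 0 and 0.01 show. This stands, as an expectation without a figure. It says nothing about age or education.
- **Most of any gain would come from covariates, not from matching the randomisation.** This stands. Practice contributes about one point of power at an ICC of 0.05. The socio-economic grouping is a grouping of practices and not a further allocation factor for men.
- **The strongest usual covariate, a baseline score, is not available.** This stands and points to a modest gain.
- **Chance imbalance is not bias.** This stands: the interval already allows for it.

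A reader might infer that precision is lost on every outcome, or that the unadjusted tests are wrong. The article supports neither. The loss is zero if practice, age and education explain nothing; the formula does not carry over to an odds ratio for uptake; and the error in the tests, where there is one, is towards caution. Nor does the article show that the demographic items are collected after randomisation; it does not say when they are collected.

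**Conclusion.** The point holds as a modest, conditional improvement in efficiency. The named analysis leaves out the stratum within which men are randomised and two recorded variables that may predict the outcomes. The planned tests remain valid and the principal outcome is not endangered.

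The size cannot be fixed from the article. For the continuous scales it runs from no gain at all to a standard error about 11% smaller at an R² of 0.20, with decisional conflict the clearest beneficiary because its planned power has no margin. These figures rest on the assumed R² and ICC ranges, a two-sided 5% level and the full 150 men per group.

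**What to change.** For the main comparisons, prespecify:

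- **Continuous scales** (knowledge, attitudes, decisional conflict, anxiety): a linear model with group, practice (fixed or random), and age and education as baseline covariates.
- **PSA uptake:** a model with the same terms, reported as a standardised risk difference with its interval.
- **Supportive analysis:** the t, chi-squared and other unadjusted tests already named.

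Use age and education as covariates only where they are pre-randomisation values, and say where they come from. This matters most for control group B, whose first questionnaire is at six months.

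The cost is a few sentences of analysis text, fixed before outcome data are seen. The sample size need not change.

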### vii) Mathematical Simulation Model

A mathematical simulation model of the effects of *Prosdex *on subsequent resource use and health outcomes will also be developed. This will use the trial outcomes, particularly PSA uptake, to model potential diagnoses and morbidity (drawing on existing best evidence [16]) and the resulting resource use and workload implications at GP practice and NHS Trust levels. For example, at GP practice level, the age distribution in a practice will be used, together with PSA take-up after the intervention, to estimate workloads and resource requirements, using appropriate sampling distributions as in the investigator's previous research.[17,18] By further sampling of GP practices within a hospital Trust locality, estimates would be made of the implications at Trust level for urological and other services. The data will be obtained for local GP practices from our network of practices who have participated in several other research studies in recent years.

## Abbreviations

PSA: Prostate Specific Antigen; GP: General Practitioner; PCRMP: Prostate Cancer Risk Management Programme; RCT: randomised controlled trial; CONSORT: consolidated standards of reporting trials.
